### Flowchart

[figure not shown]

The above flowchart details the RAPHE trial algorithm of subject inclusion/exclusion, allocation, randomization, and clinical procedures. Specifics of all three arms are displayed along with the required post-operative and follow-up measures.

## Discussion

TRA has taken shape as the preferred approach to invasive coronary diagnostics and is also routinely used for all forms of contemporary PCI. The method is well established and favorable by most patients and healthcare providers, although important clinical hindrances are to be noted. The available data lead us to assume, that consideration toward preservation of radial artery integrity varies on quite large of a scale. Published meta-analysis data exhibits RAO ranges from < 1 to 33%, leading us to believe that many interventional establishments do not commit adequate resources and/or manpower to preserving the radial artery, while other institutions have dedicated personnel, post-operative observation rooms and in-house guidelines to maximize radial artery patency (4). As an important clinical part of DOCE, the established protocol of the RAPHE trial strongly focuses on preserving radial artery patency in all three arms. We expect RAO will be between 3 and 5% in all three arms of the RAPHE trial, with hopes of achieving a value of less than 3%.

Another component of DOCE, RAD is reported at surprisingly scarce frequencies. We strongly believe that this is due to the fact, that studies, incorporating detailed post-operative ultrasound evaluation are seldom, thus these phenomena appear massively underreported. With PH MCD use and non-compression based hemostasis devices we are of the opinion that RAD will definitely play a significant role in DOCE frequencies, maybe even occurring at a higher overall percentage than RAO. Thus, we expect an overall RAD rate (encompassing artery dissection, (pseudo)aneurism, and fistula formation) of between 5 and 8% with our rigorous sonographic follow-up evaluations.

Bleeding from the radial puncture site although less common as compared to femoral or brachial approaches still occurs at a clinically significant rate. Luckily, most bleeding issues do not require specific medical therapies, although they may be a cause for distress in patients especially when accompanied by discomfort and edema formation, which require topical care and pain alleviating medication. Serious, EASY III-V grade bleeding requiring specific, mostly surgical treatment occur rarely (< 1%) (17). Overall, clinical hematoma formation, assessable on the EASY scale (I-IV) is expected at around 5–7% in the RAPHE trial, with the majority (> 80%) of cases expected to be EASY class I and II.

RAPHE will focus on RAO, RAD and bleeding equally, from a device-oriented endpoint as all present clinical challenges influence quality of life of patients. With RAO, a conduit for further use is eliminated and clinical signs of upper extremity ischemia may present, necessitating surgical or endovascular treatments. Damage to the radial artery, clinically mostly manifesting as (pseudo)aneurysm and fistula formation can cause substantial pain/discomfort, paresthesia and even a palpable mass above the site of the puncture often causing a thrill in case of an arterio-venous fistula. These pathologies will likely require interventional methods or surgical repair to avoid chronic vascular conditions (5–8) and may cause a notable decrease in quality of life if left unchecked and/or untreated. Bleeding as the most common complication after TRA if serious may present as a significant or even critical issue. Thus a “perfect” compression device has a DOCE of zero per cent, as it causes no bleeding, RAO or RAD. In the RAPHE study we expect an overall DOCE rate, encompassing everything above of around 15% in all three arms of the trial.

The main goal of the study will be to determine, how standalone bioactive chitosan and/or potassium ferrate devices fare against the gold standard pneumatic airbladder based MCD. Besides clinically relevant safety and efficacy profiles, we will opt to also explore if fewer human resources are required to manage said bioactive devices. As per the RAPHE protocol, bioactive devices only require one adjustment, shortly after application and may require less overall compression time. Reducing the need for extensive human resource PH management and continuous MCD adjustments in high-volume centers is favorable, due to a multitude of factors. As bioactive devices do not require adjustments every 10–20 min, additional staff, managing strict PH protocols may be allocated elsewhere. In the RAPHE study we assume that patients randomized into one of the two investigational arms (potassium ferrate disc or chitosan sponge) will achieve primary hemostasis quicker and require less overall compression time as compared to MCD control subjects. From an economic point of view, the RAPHE trial will also be assessing the need of hemostasis units per patient in all three arms, and record if bail-out compression devices are needed. We have no convincing assumptions regarding these endpoints, due to a lack of prior reported data or in-house registries.

### Ethics and Dissemination

#### Ethical Considerations

The RAPHE clinical trial will be conducted in accordance with good clinical practice and the Helsinki Declaration (25). All regulatory and notified body requirements have been met to perform the study. The RAPHE study has been cataloged and authorized by the Hungarian National Institute of Pharmacy and Nutrition under number: OGYÉI/13123/2021. All enrolled patients will provide a written informed consent form, prior to any enrollment, study procedure or randomization, which will be collected by certified physicians participating in the study.

#### Safety and Termination

A Data Safety Monitoring Board (DSMB) consisting of three independent physicians who are not part of the RAPHE trial will perform an interim analysis after 50% of patients have been enrolled into a study. The DSMB will assess if any novel treatment option proves superior or inferior to the MCD used as the control. Statistical design will permit an early termination of the study if the DSMB identifies any potential advantages or disadvantages in any of the hemostasis options.

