### Endpoint Definitions and Hypothesis

The primary endpoint of the study will be a device oriented complex endpoint (DOCE). A complex endpoint has been defined, to assess hemostasis devices from both important clinical viewpoints: its efficacy in containing puncture site bleeding and its safety in terms of preserving radial artery patency and integrity.

DOCE will encompass the following: post-operative bleeding with visible hematoma formation after hemostasis device removal classified using the EASY methodology (17) (I), RAD, encompassing vessel dissection, (pseudo)aneurism and/or fistula formation (II) and RAO (III). These three parameters will be measured and quantified first at 24 hours after hemostasis device removal or at hospital discharge (whichever comes sooner), and again assessed at the 60-day follow-up visit.

Secondary endpoints will focus on human resource requirements and economics of devices. These include initial compression to achieve primary hemostasis (I), overall compression device usage time (II), and number of compression devices needed (III). Primary hemostasis is defined as the time in minutes, from application of the hemostasis device to the first successful decrease of the initial torniquet pressure, with success indicating no repeat bleeding from the puncture site. Overall compression time refers to total time of devices used as a hemostasis tool. In cases of acute bleeding following device use, a new, freshly opened tool may sometimes be required if the first one failed to contain bleeding. According to the RAPHE protocol, in case of initial device failure, a second, identical tool is to be utilized. If the second device also fails to contain puncture site bleeding, a bail-out hemostatic device will be employed. Thus, our last tertiary endpoint has been defined as follows: the need for a bailout compression method (I).

We hypothesize, that utilizing either of the novel bioactive devices in a standalone arrangement will prove clinically non-inferior to the other study and the control MCD, respectively. Furthermore, we assume, that the use of either one of the standalone bioactive devices will require less compression time, fewer human resources, and less management to successfully handle as compared to the MCD.

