### Sample Size Calculation

Sample size calculation was carried out for non-inferiority studies following established guidelines (18, 19) with a significance level of 95% and a power of 80%. Although the best reported component of the DOCE, RAO rates range from < 1 to 33% (4), and it would be advisable to estimate sample size calculations for the worst-case scenario (i.e., 33%), however analyses of our own existing data regarding RAO and RAD (The RadPress trial—unpublished) deemed this value unreasonable for the centers involved. Therefore, we used a conservative 15% of the population rate for the DOCE for both intervention and control treatments. We allowed a 10% relative inferiority margin for the investigated treatments (20). The resulting sample size was 158 patients per arm. We also accounted for a potential 10% drop-out rate and factored in the uncertainty in true DOCE rates, and hence sample size estimates, and thus rounded the sample size to 200 patients per arm.

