### Statistical Analyses

Data analysis will be done on an intention to treat basis. Baseline patient and disease characteristics will be summarized with detailed descriptive statistics that entail mean, median, SE, SD, IQR and range for continuous variables, while for categorical variables absolute and relative frequencies will be reported. Hypothesis testing of the primary outcome will be done with Fisher’s exact test with a significance level of 95%. Univariate analyses of secondary endpoints will be carried out as superiority analyses with one-way ANOVA, Kruskal-Wallis test, or logistic regressions, depending on the outcome variable type and distribution. Multivariate analyses of secondary endpoints will entail using general or generalized hierarchical mixed effects models depending on variable type and distribution. All statistical analyses will be done in the R statistical environment (21).

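### The interim rule permits ending the whole study on any potential advantage or disadvantage of any device, with no evidential threshold and no allowance in the final test level or the sample size

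*Protocol article*

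**What the plan says.** Under Safety and Termination, the article says that a DSMB of three independent physicians "will perform an interim analysis after 50% of patients have been enrolled into a study". The task at that look is then described: "The DSMB will assess if any novel treatment option proves superior or inferior to the MCD used as the control". The next sentence gives the stopping criterion: the design will "permit an early termination of the study if the DSMB identifies any potential advantages or disadvantages in any of the hemostasis options".

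Three other sections bear on this:

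- **Endpoint Definitions and Hypothesis.** The hypothesis is that either bioactive device "will prove clinically non-inferior to the other study and the control MCD, respectively". The primary endpoint, the DOCE, is assessed at 24 hours or discharge and again at 60 days.
- **Sample Size Calculation.** The calculation is for non-inferiority, "with a significance level of 95% and a power of 80" per cent, and "we used a conservative 15% of the population rate for the DOCE for both intervention and control treatments". The result is 158 per arm. It is raised to 200 for drop-out and for uncertainty in the true rate; the interim look is not among the reasons.
- **Statistical Analyses.** The primary outcome is tested with Fisher's "exact test with a significance level of 95" per cent. No reduction for the interim is mentioned.

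**The concern.** Two consecutive sentences set different standards. The first asks whether a device is proved better or worse than the control. The second lets the study end on a potential difference in either direction, for any of the three options. A DSMB that follows the second sentence needs no particular strength of evidence.

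Three consequences follow.

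- If an early stop for an apparent advantage is reported as a positive result, the data have had two chances to succeed while the final test still uses its full level.
- If the study stops on a chance difference, it ends with about half its patients and may be unable to answer the non-inferiority question. The interim assessment, as described, does not ask that question.
- The permission is to end the study, not an arm. A signal in one bioactive device could therefore also end the comparison of the other device with the control.

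The trigger is enrolment. Patients enrolled shortly before the look will not yet have their 60-day assessment, so the information at the look is at most one half of the total.

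**Working it through.** **Inputs.** From the article: 600 patients randomized 1:1:1, so 200 per arm; a look at 50% enrolment, so about 300 patients or 100 per arm; DOCE 15% in all arms; power 80%; a 5% level; 158 per arm before the increase to 200. Two inputs are inferred from the 158: a margin of 10 percentage points absolute (the text calls the margin relative) and a one-sided 0.05 test (sidedness is not stated).

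**1. Reproducing 158.** For equal rates,

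n = (z₁₋α + z₁₋β)² × 2p(1−p) / Δ²

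= (1.645 + 0.842)² × 2 × 0.15 × 0.85 / 0.10² = 6.183 × 25.5 = 157.7, so 158.

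This matches exactly. One-sided 0.025 would give 201. A margin of 10% relative (1.5 points) would give 7007 at one-sided 0.05. The 158 is thus a fixed-design number with all of the alpha spent at the final analysis.

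**2. Error rate with an unadjusted look.** At half the information the interim and final statistics have correlation √0.5 = 0.707. The probability that at least one exceeds its critical value under the null is 1 − Φ₂(c, c; 0.707).

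| Test used at both looks | Final look only | Either look |
|---|---|---|
| One-sided 0.05, normal theory | 0.050 | 0.080 |
| One-sided 0.025, normal theory | 0.025 | 0.042 |
| Two-sided 0.05 z-test of equality, simulated at 15% | about 0.05 | 0.085 |
| Two-sided 0.05 Fisher test of equality, simulated at 15% | 0.036 | 0.058 |

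The first row fits the design that reproduces 158. A binomial simulation at the non-inferiority margin (25% against 15%) agrees with it: 0.051 at the final look only and 0.082 at either look for one device. The last two rows concern equality, not non-inferiority.

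**3. How large chance differences are at the look.** With 15% in both arms and 100 per arm, the standard error of a difference is

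√(2 × 0.15 × 0.85 / 100) = 0.0505, or 5.0 points,

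and the 95% half-width is 1.96 × 0.0505 = 0.099, or 9.9 points. With three truly identical arms, simulation gives the chance that at least one bioactive device differs from the control:

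| Observed difference, either direction | Share of trials |
|---|---|
| 3 points or more | 84% |
| 5 points or more | 57% |
| 10 points or more | 11% |

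**4. Power if the study ends at the look.** Power = Φ(Δ/SE − z₀.₉₅) = Φ(0.10/0.0505 − 1.645) = Φ(0.335) = 0.63. This assumes that all 100 per arm are evaluable and uses the same margin and one-sided 0.05. The design aims at 0.80.

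**5. The price of a proper boundary.** O'Brien-Fleming limits that hold one-sided 0.05 over two equally spaced looks are Z = 2.37 at the interim (p = 0.0088) and Z = 1.68 at the final (p = 0.0467). The requirement rises from 158 to about 161 per arm. Power is about 84% with 180 evaluable per arm (200 less 10%) and about 87% with 200.

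**The case against.** The strongest reply is that stopping boundaries, alpha spending and the deciding interim endpoint usually sit in an SAP or DSMB charter, and that this is a condensed article. That stands: a missing boundary alone would be no finding. The difficulty is with what is written. The article states a criterion, and any charter with a real boundary would contradict it.

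A reader might infer more than the documents support.

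- **That the DSMB must stop on any signal.** The wording permits termination and does not require it. The preceding sentence also sets a stricter standard. The fault is the absence of a threshold and the conflict between the two sentences.
- **That the look produces false-positive rates of about 15% or 20%.** Two unadjusted z-test looks give about 15% over the two comparisons with the control and 20% over all three pairs. But 9.2% and 12.5% are already present with no interim, from ordinary multiplicity. The stated interim assessment covers only the comparisons with the control. These rates also measure error for equality, and they count apparent harm as a false positive. With the planned Fisher test the rate per comparison is 5.8%.
- **That every early stop inflates error.** Only stops for advantage that lead to a positive claim do so. Stops for disadvantage cost power.
- **That many of the 300 will lack the 60-day DOCE.** Some must, but how many depends on an accrual rate that the article does not give. The 24-hour or discharge assessment should be available for nearly all.
- **That the sample size is too small to carry an interim look.** At one-sided 0.05 it is not, as step 5 shows.

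**Conclusion.** The concern holds in this form: the article permits the whole study to end at 50% enrolment on a criterion with no evidential threshold. That criterion conflicts with the sentence before it and does not address the non-inferiority hypothesis, and neither the final test level nor the 158 per arm allows for the look.

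If an unadjusted interim advantage counts as success, a one-sided 0.05 error becomes about 0.080 per comparison; a looser threshold would give more and a strict one less. If the study stops at the look, non-inferiority power is at most about 63%. With identical devices, a 5-point difference for at least one of them is more likely than not.

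These figures assume a 15% DOCE rate in all arms, a 10-point absolute margin, one-sided 0.05, and 100 evaluable patients per arm at the look. The actual inflation cannot be fixed, because the threshold that the DSMB would use is not stated.

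**What to change.** In Safety and Termination, and in the DSMB charter, before the DSMB sees any comparative data:

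1. Replace the criterion of any potential advantage or disadvantage with a prespecified boundary on the DOCE, applied to each bioactive device against the control. State that a signal in one device does not by itself end the other comparison. Reconcile the two sentences so that they set one standard.
2. Choose one of two routes for advantage and non-inferiority. Either allow no such stop at the interim, so that the final test keeps its level; or use a group-sequential limit matched to the design alpha. For O'Brien-Fleming at one-sided 0.05 that is about Z 2.37 at the interim and 1.68 at the final. Limits of 2.80 and 1.98 belong to two-sided 5%; adopting them would change the alpha behind the 158 and leave about 75% power at 180 evaluable per arm.
3. Tie the look to the number of patients with the deciding DOCE assessment complete, not to enrolment.
4. Leave stopping for harm to the DSMB's safety judgement and to a harm criterion that the sponsor defines. An efficacy-style limit such as p < 0.001 should not be imposed on it: at 100 per arm it would detect a true doubling of the DOCE from 15% to 30% only about 22% of the time.

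The cost is wording in the protocol and charter, a smaller chance of stopping early on an apparent advantage, and a slightly later look. No increase over 200 per arm is needed at one-sided 0.05.

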#### Data Management

All patient and procedure data will be stored on independent, encrypted, username and password protected servers with access restricted to study and DSMB personnel.

## Ethics Statement

The studies involving human participants were reviewed and approved by Hungarian National Institute of Pharmacy and Nutrition under number: OGYÉI/13123/2021. The patients/participants provided their written informed consent to participate in this study.
